### Cost-effectiveness analysis

The evaluation of cost-effectiveness will utilize depression scores as the primary metric. Depending on the accessibility of data, these scores will be connected to long-term indicators such as Quality-Adjusted Life Years (QALYs) or Disability-Adjusted Life Years (DALYs). This linkage will be facilitated through methodologies like WHO-CHOICE and the WHO's estimators for DALYs and QALYs (68). Adjustments will be applied to guarantee precision for factors like inflation, exchange rate fluctuations, and the discounting of both costs and outcomes.

The WHO-CHOICE (Choosing Interventions that are Cost-Effective) framework is designed to assess the cost-effectiveness of healthcare interventions by examining their effects on disease burden and related costs, providing a standardized yet adaptable approach for various health settings and conditions. Meanwhile, the WHO's DALY/QALY estimator measures the disease burden and the efficacy of health interventions in Disability-Adjusted Life Years (DALYs) or Quality-Adjusted Life Years (QALYs), taking into account both the years lost due to premature mortality and the years lived with disability or illness. These tools are invaluable for healthcare policymakers, aiding in the strategic allocation of resources and the development of cost-effective healthcare strategies.

To assess the cost-effectiveness of various service delivery models, our analysis will be aligned with established benchmarks, such as GDP per capita or findings from analogous studies in similar contexts. Throughout the study, we will comply with the economic evaluation principles outlined by the second panel on cost-effectiveness (69) and adhere to the CHEERS guidelines (70) for transparent and standardized reporting of our results.

### Ethical considerations

This study will seek approval from Makerere College of Health Sciences Research Ethics Committee and the Ugandan National Council of Science & Technology (UNCST). Researchers will gain full consent from hospital and community leadership prior to conducting the study. All participants will be required to give full informed consent to take part, and all identifying information fully anonymised in reporting. This trial is registered with The Pan African Clinical Trials Registry.

## Results

### Trial status

The Makerere School of Health Sciences Research Ethics Committee and the Uganda National Council of Science and Technology have granted approval for the trial. Recruitment commenced in May 2023 and concluded in July 2023, successfully enrolling 300 youths aged 15–30 years with mild to moderate depression levels. In parallel with the recruitment, TMCG developed the telepsychotherapy call platform. Those participants were randomly assigned to two groups: 154 were instructed to use their mobile phones to call the tele-psychotherapy platform to receive both Tele-support psychotherapy (TSP) and also to go to the nearest mental health treatment center for Standard Mental Health Services (SMHS) if their depression symptoms do not improve, and 146 were instructed to go to the nearest mental health treatment center and seek SMHS only. Currently, the analysis of data collected at the baseline is underway. The findings from this study are slated for presentation at both national and international forums. Efforts are also being made to draft manuscripts for submission to peer-reviewed academic journals, and comprehensive reports will be compiled for the funding body.

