**Methods and analysis:**

This study will use a mixed-methods approach, starting with a qualitative phase to adapt Group Support Psychotherapy into Tele-Support Psychotherapy (TSP) via mobile phones. Guided by ecological theories and the Unified Theory of Acceptance and Use of Technology (UTAUT), focus group discussions and interviews with youth, mental health professionals, and stakeholders will inform the development of a youth-tailored call platform integrated into Rocket Health Africa's telehealth services. Data will be analyzed using grounded theory and MAXQDA Analytics Pro 2022 to guide intervention adaptation. An open-label randomized controlled trial will enroll 300 youth (15–30 years) with mild to moderate depression from Kampala, Uganda, to evaluate Tele-Support Psychotherapy (TSP). Participants will be randomized to TSP with standard mental health services (SMHS) or SMHS alone. Primary outcomes include feasibility and acceptability, with secondary outcomes assessing cost-effectiveness, depressive symptom changes, and social support. Intention-to-treat analysis using structural equation modeling will evaluate treatment effects, complemented by qualitative insights into implementation barriers and facilitators.

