In the trial phase, we shall conduct a pilot single-blinded randomized controlled trial to test the feasibility and

acceptability of using TSP in combination with standard mental health services(SMHS) vs. SMHS only to treat mild to moderate depression among youth in Kampala district. We aim to randomize 300 youth (1:1) to either both TSP and SMHS (*N* = 150) or SMHS only (*N* = 150). The 150 subjects in each arm will be recruited from three communities (Makerere University (*N* = 50), Kamwokya slums (*N* = 50) and Naguru go-down slums (*N* = 50) in each treatment arm and invited to participate. Participants will be evaluated at baseline, 6 and 12 months after baseline assessment.

A longitudinal process evaluation of the delivery of TSP using mobile phones and SMHS using mixed methods will run alongside the trial to assess acceptability, feasibility, fidelity, barriers and facilitators and how intervention recipients respond to the different intervention components. Open-ended exit interviews with recruited trained lay counsellors and study participants will seek to understand stressors in their communities, their own psychosocial support needs, and their knowledge regarding mental health after training, satisfaction, barriers and facilitators of participation in TSP sessions. Attendance registers and training logs will be used to track indicators of feasibility.

The study protocol is registered in the Pan African Clinical Trials Registry. The reporting of the trial will be in accordance with the Standard Protocol Items: Recommendations for Interventional Trials (SPIRIT) guidelines (39) for intervention trials (see Supplementary File S1) and the CONSORT statements for pilot randomized trials (40). The study was submitted to and approved by both the Makerere University College of Health Sciences Research Ethics Committee and the Uganda National Council of Science and Technology. All study participants will be required to provide written informed consent. Participants will receive a financial incentive to compensate for their time and defray internet data costs (if any). Figure 1 summarizes the trial profile.

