#### Feasibility

Indicators of feasibility will be assessed by determining the proportion of eligible participants who engage in either intervention (reach), the proportion who attend all 8 sessions of either intervention (dose delivered), and the proportion lost to follow-up (attrition), using data from attendance registers.

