### Determining cost-effectiveness

To assess the cost-effectiveness of providing TSP with SMHS vs. the provision of SMHS alone, we will adopt a societal perspective in our analysis. This approach encompasses not only the direct costs associated with the interventions—such as program delivery expenses—but also indirect costs like those stemming from the use of additional healthcare services and the loss of productive time due to participation in the interventions. We plan to devise a comprehensive questionnaire to gather detailed information on the utilization of supplementary healthcare resources, including visits to medical professionals covered by insurance, outpatient services, and expenditures on mental health medications, which may be influenced by the intervention.

The financial implications of implementing both the TSP & SMHS combination and the SMHS-only model will be meticulously calculated, focusing on contrasting these costs against the respective outcomes each model achieves, particularly regarding depression score improvements. It's crucial to clarify that the expense of conducting the research and any ancillary research activities, will be excluded from the cost-effectiveness evaluation.

Moreover, we intend to delve into the economic repercussions associated with time loss for different participant groups, including those volunteering without compensation, and the additional burden placed on individuals due to increased responsibilities linked to the study. To quantify these indirect costs, we will employ shadow pricing techniques. The identification of costs will be primarily based on project documentation and financial reports. For any costs not directly documented, we will turn to existing literature for estimates. Significant expenses related to services and procurements will be determined by the terms of reimbursement contracts or, in certain cases, prevailing market rates at the time of acquisition. Additionally, we will leverage databases such as the Uganda Bureau of Statistics (UBOS) to source pertinent data to inform our cost-effectiveness analysis, ensuring a robust and comprehensive evaluation of the interventions’ economic viability.

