We will assess randomization across the two arms by comparing socio-demographic characteristics and other potential confounding variables using chi-square for categorical variables and t-tests or other equivalent nonparametric tests, as appropriate, for continuous variables. Secondary outcomes will be the difference in follow-up mean depression, anxiety, stigma and social support scores between TSP-SMHS and SMHS (Control group) participants. These outcomes will be analyzed by ITT using generalized structural equation modelling. The STATA 16 statistical software will be used to conduct all analyses. Missing values will be imputed with multiple imputations.

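### The Methods give the TSP arm SMHS without condition, but the trial status makes SMHS conditional on non-improvement, so the add-on label on the secondary and cost contrasts may not match what was assigned

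*Protocol article*

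**What the plan says.** The design sections agree with one another:

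- Abstract, Methods and analysis: "Participants will be randomized to TSP with standard mental health services (SMHS) or SMHS alone".
- Study design: the aim is to "randomize 300 youth (1:1) to either both TSP and SMHS", with the other half allocated to SMHS only.
- Statistical analyses: the secondary outcomes are differences in follow-up means "between TSP-SMHS and SMHS (Control group) participants", analysed by intention-to-treat.
- Determining cost-effectiveness: the comparison is "the cost-effectiveness of providing TSP with SMHS vs. the provision of SMHS alone".

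The end of the Introduction says the data will help to design a definitive trial, whose hypothesis is that TSP on top of SMHS reduces depressive symptoms more than SMHS by itself.

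Trial status then reports what participants were told. Those in the TSP arm were to use the call platform and "also to go to the nearest mental health treatment center for Standard Mental Health Services (SMHS) if their depression symptoms do not improve". In the control arm, "146 were instructed to go to the nearest mental health treatment center and seek SMHS only".

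**The concern.** The two accounts describe different experimental strategies. In the first, both arms have SMHS on the same terms and differ only in TSP, so the contrast is the effect of adding TSP. In the second, the TSP arm starts with TSP and moves to SMHS only on non-response, while controls are directed to SMHS from the start. The arms then differ in two ways: whether TSP is offered, and the terms on which SMHS is recommended.

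What is at stake is the meaning of the secondary-outcome and cost results. Under the label TSP-SMHS versus SMHS, a reader will take them as the increment from TSP over usual care. If the conditional instruction was really given, they describe a stepped strategy. SMHS use also enters the cost of each arm directly, so the cost comparison depends on which strategy was run. The definitive trial is framed as an add-on question, so a stepped-care result could be taken forward under the wrong name.

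**Working it through.** This is a comparison of texts. The only figure in the article that can be reproduced is the enrolment: 154 + 146 = 300, as stated.

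**1. Is there a condition on SMHS, by arm and by section?**

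| Section | TSP arm | Control arm |
|---|---|---|
| Abstract | SMHS, no condition | SMHS |
| Study design | SMHS, no condition | SMHS |
| Determining cost-effectiveness | SMHS, no condition | SMHS |
| Statistical analyses | SMHS, no condition | SMHS |
| Trial status | SMHS if no improvement | SMHS, no condition |

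The condition appears once, and only for the TSP arm.

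**2. Does another section supply the condition?** The only conditional referral in the Methods is under Adverse event management. It sends participants to hospital mental health departments when suicidal ideation persists after four counselling sessions. That is a safety rule with a different trigger, so it does not explain the Trial status wording.

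**3. What does intention-to-treat estimate?** It compares the strategies as assigned. Under the Methods wording that is TSP plus SMHS against SMHS. Under the Trial status wording it is TSP with step-up SMHS against SMHS. Both are valid randomised comparisons; only the name of the second would be wrong.

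**4. Can the gap between the two be sized?** No. It depends on how many people use SMHS in each arm, how much SMHS helps those users, and how much of any difference in use arises from the differing instruction. The article gives none of these. The last matters because TSP participants who improve might seek less SMHS even under identical instructions, and that difference belongs to a pragmatic add-on effect. A calculation that counts every difference in uptake as error would therefore measure the wrong thing, and its sign would depend on the assumptions chosen.

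**5. Can SMHS use be compared by arm?** Yes, if it is recorded. The 95% half-width for a difference between two proportions is widest at 50% in each arm: 1.96 × √(0.25/154 + 0.25/146) = 0.113, about 11 percentage points. With an assumed 20% attrition it is 0.127, about 13 points. A large difference in uptake would be visible.

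**6. Is it recorded?** The planned healthcare-use questionnaire covers "outpatient services, and expenditures on mental health medications, which may be influenced by the intervention", which is close to what is needed, but SMHS visits are not a named item. The attendance registers serve feasibility indicators such as "the proportion of eligible participants who engage in either intervention (reach"; the article does not say whether they capture visits to SMHS clinics.

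**The case against.** The best defence is that this is one badly built sentence in a short status summary, set against consistent design text. The sentence promises that participants will receive both things and then never completes the pair, so it may simply be a slip for the two-component arm. That is possible, and it limits confidence in the finding. However, the conditional clause is specific and has no counterpart for controls, so it cannot be dismissed without checking.

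A second defence is that SMHS is usual care for those who seek it. The section on SMHS fixes no dose, and the awareness campaign described under Recruitment told all prospective participants about SMHS. TSP with SMHS could then mean TSP plus access to usual care. This narrows the gap but does not close it, because the recommendation about SMHS still differs by arm. The Feasibility section, which speaks of attending all eight sessions of either intervention, also fits this reading poorly.

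Third, this is a pilot. Effectiveness and cost-effectiveness are called exploratory, and Sample size estimation disclaims any aim of proving superiority. That stands and limits the consequences.

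A reader might infer more than the article supports:

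- That the intention-to-treat analysis is invalid. It is valid for the strategies assigned.
- That the benefit of TSP will be understated by some definite amount. Neither the sign nor the size is available.
- That the pilot's effect size is set to be used as the add-on effect in the definitive trial. The article says the data will inform that trial and seeks parameter estimates, but the only parameter it discusses is the variance.

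**Conclusion.** The inconsistency is real and unresolved within the article. It bears on the label and interpretation of the secondary-outcome and cost contrasts, provided the Trial status sentence describes the instruction actually given. If that sentence is a slip, the finding reduces to a correction of wording. No magnitude can be attached.

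The primary feasibility and acceptability outcomes and the variance estimate sought from the pilot are not materially affected. Confidence is medium, because everything turns on one loosely worded sentence. The point merits action because the remedy is small and the add-on question is the one named for the next trial.

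**What to change.** 1. Check the instructions given to participants, for example in the participant materials or the counsellors' and research assistants' guides.
2. If SMHS was conditional in the TSP arm, describe the arm that way, label the secondary-outcome and cost contrasts as TSP with step-up SMHS versus SMHS, and do not present them to the definitive trial as the effect of adding TSP to SMHS.
3. If SMHS was not conditional, correct the Trial status sentence.
4. In either case, report SMHS use by arm at 6 and 12 months, mainly from the healthcare-use questionnaire, making sure it includes SMHS visits and mental health medication. Use the attendance registers only if they prove to record clinic visits.

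The cost is some wording and one descriptive table. Recruitment closed in July 2023, so the instructions cannot be changed. Twelve months on is July 2024, before the article appeared in February 2025, so follow-up may already be complete. If SMHS visits were not asked about, the report should say so. The substantive downside is that the add-on label may have to be given up for these exploratory results.

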## Discussion

This study is expected to demonstrate the feasibility, acceptability, and preliminary effectiveness of Tele-Support Psychotherapy (TSP) delivered by lay counsellors via mobile phones to address depression among youth in Kampala, Uganda. By leveraging mobile health (mHealth) technologies, the intervention is anticipated to provide a scalable, accessible, and cost-effective mental health solution tailored to resource-limited settings. A key component of the study will be the development of a call platform, enabling youth with depression to connect with lay counsellors who will deliver eight sessions of therapy via mobile phones. Additionally, the integration of the Ecological Validity and Culturally Sensitive Framework is anticipated to enhance user engagement and ensure cultural relevance (71).

Other protocols have proposed single-session apps, gaming apps and virtual reality as digital mental health interventions for youth in sub-Saharan Africa. Osborn et al. explored the effectiveness of two digital single-session interventions (Shamiri-Digital and Digital-CBT) among Kenyan adolescents (11). While these single-session interventions show promise for scalability and accessibility, their practicality may be limited for addressing complex mental health issues like mild to moderate major depressive disorders, as effective problem-solving often requires emotional regulation—a process that takes time to develop (72).

In contrast, this protocol proposes a more practical and realistic approach by offering eight therapy sessions via mobile phones. The multi-session structure allows for a gradual and comprehensive therapeutic process: session 1 focuses on building rapport between the client and therapist, sessions 2 prepares the brain through psychoeducation, sessions 3 and 4 facilitate the release of strong emotions, and sessions 5 and 6 introduce positive coping strategies such as problem-solving. Sessions 7 and 8 further equip participants with income-generating skills to enhance resilience. This stepwise approach ensures that participants achieve emotional regulation before moving on to problem-solving, offering a more robust and sustainable therapeutic outcome.

Moreover, this protocol goes beyond the interventions of Shamiri-Digital and Digital-CBT by addressing barriers faced by underserved youth living in extreme poverty. Unlike smartphone-based apps, which may not reach those without advanced devices, this protocol includes the development of a call platform that will enable youth with basic phones to connect with lay counselors for therapy. Additionally, it will build mental health capacity by training lay counselors to deliver the intervention, creating a sustainable support system within the community. By addressing contextual and infrastructural limitations, this protocol offers a more comprehensive and inclusive solution tailored to the realities of resource-limited settings.

Our proposed study offers key advantages over other studies using gamified mental health apps (12). Unlike the apps, which rely on smartphone access and provide brief, self-guided behavioural activation, TSP will use a call platform accessible to youth with basic phones, ensuring broader reach among underserved populations. TSP sessions will be similar to GSP sessions with the goal of delivering a comprehensive therapeutic process, addressing emotional regulation, psychoeducation, coping skills, and resilience-building, which is more practical for managing complex mental health issues. Additionally, TSP will incorporate human interaction through trained lay counselors, fostering trust and adaptability, and will employ a rigorous mixed-methods evaluation to assess both feasibility and acceptability and effectiveness and contextual mechanisms. This inclusive, scalable approach positions our TSP intervention as a potentially more impactful and sustainable solution for youth mental health in resource-limited settings.

Similarly, our protocol offers advantages over virtual reality (VR). For example, the Mobile Health–Supported Virtual Reality and Group Problem Management Plus (PM+) protocol by Logie et al. (4) also targets urban youth but relies on VR and group-based PM + therapy (73). While VR may be less accessible to youth living in extreme poverty, our TSP study will use a call platform compatible with basic phones, ensuring it can reach a broader audience. TSP prioritizes scalability and cost-effectiveness by leveraging simple mobile technology and training lay counsellors, making it better suited for addressing depression among diverse youth populations in low-resource settings.

This study's findings can potentially transform mental health care delivery in low- and middle-income countries (LMICs). By demonstrating the viability of tele-psychotherapy, this research could inform policies and guide the integration of digital mental health interventions into primary care systems. The anticipated success of the TSP model could help bridge gaps in mental health care access, reduce stigma, and address provider shortages in resource-constrained settings. Furthermore, the study could lay the groundwork for scalable, cost-effective, adaptable digital interventions across diverse cultural and socio-economic contexts.

Several limitations must be acknowledged. As a pilot randomized controlled trial (RCT), the findings may have limited generalizability to broader populations. Challenges such as inconsistent network access, varying familiarity with digital tools among participants, and cultural factors influencing acceptability may affect recruitment, retention, and adherence to the intervention. Additionally, the reliance on self-reported measures for outcomes and use of measures with low predictive values such as the SAD PERSONS scale (74) may introduce bias.

